### ***Enrolment***

At enrolment, consenting participants will receive the MHM intervention including MHM education, analgesics, 2 pairs of period pants, and all the MHM products in Table 5. Participants will also be asked to complete a self-administered structured quantitative questionnaire using ODK on a tablet to obtain data on socio-demographics, and genital and menstrual hygiene, knowledge on menstruation and MHM, MHM perceptions and practices, pain management, and psycho-social well-being. Each participant will also be given a comprehensive 4 month period tracking diary. The participants and RAs will also go through the participants' period tracking diaries together to make sure participants are comfortable and confident using the diaries and that the diaries are being completed accurately on a monthly basis.

Participants will also be given a participant booklet with the dates of their follow up visits (with a two-week window period around their scheduled follow-up visit date). If participants fail to attend their CHIEDZA site visit, they will be contacted and asked if they can be visited at home.

### ***Follow-up***

Participants will be followed up every 3 months for one year. At baseline, 6 months, and at 12 months (endline), participants will complete the same self-administered quantitative questionnaire to obtain updated data on genital and menstrual hygiene, MHM knowledge, perceptions, and practices, psycho-social well-being and period pain management knowledge. At the first 3-month follow-up visit, the first period tracking diary will be collected. Participants will be given another 4 month period tracking diary at the 9 month visit that will be collected at the 12 months visit.

If participants fail to make their scheduled CHIEDZA site visits they will be contacted via phone (up to three times). If participants fail to reschedule their

follow-up visit at the CHIEDZA site or then choose to have a home visit, a trained research assistant will travel to participant's home, according to the address given. If the participant is not at home on the date of the scheduled visit, they will be contacted via phone (up to three times).

### ***Sample Size***

A sample size is based on Objective 3: 300 participants will provide 90% power to detect an increase in adequate HM practices from 10% to a double of 20% before (pre-) and after (post-) the intervention for each sub-study participant respectively.

### ***Statistical Methods***

Descriptive statistics will be used to show the socio-demographic characteristics as well as the distribution of knowledge, perceptions and practices regarding MHM. The self-reported MHM practices will be used to generate a pooled, aggregate of adequate MHM modified from the Joint Monitoring Program of the WHO and UNICEF in 2012. The MHM sub-study intervention will only affect three components of the definition: access to clean absorbents including, when relevant, sufficient washing, drying, storage and wrapping of reusable absorbents; adequate frequency of absorbent change; and basic understanding of menstruation. The intervention will not affect washing the body with soap and water; adequate disposal facilities; or privacy for managing menstruation.

McNemar's test for correlated proportions and conditional logistic regression will be used to compare the proportion with improved MHM practices (Objective 3), proportion with good knowledge and appropriate perceptions (Objective 4), and appropriate pain management (Objective 5) pre- and post- the intervention.

Data from all of the period tracking diary entries will be used for descriptive statistics on MHM product choice and continued or discontinued product use over time, and MHM product patterns of use, MHM practices and pain management during menstruation (Objectives 2, 3, and 5). The diary entries will also track if participants missed work or school on the days before, after, or during their periods.

The facilitators, barriers, reasons for MHM product choice and continued and discontinued use of products over time and an appraisal of MHM products from participants will be further explored using qualitative methods.

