## ii. 5.4.2 Study Aim and Objectives

The aim of the MHM sub-study is to investigate the acceptability, uptake, and effectiveness of an MHM intervention within the community-based CHIEDZA trial among women aged 16-24 years.

The specific objectives are

1. To understand and describe the current knowledge levels, practices and perceptions around menstruation and MHM among women aged 16 – 24 years in Zimbabwe.
  2. To investigate menstrual product choice, continued use or discontinuation of products, and patterns of use over time among young women offered all 3 product choices
- Effectiveness
3. To investigate the effect of the intervention on MHM practices e.g. access and use of clean absorbents, sufficient washing, drying, storage and wrapping of reusable absorbents; washing the body with soap and water
  4. To investigate the effect of the MHM intervention on the knowledge and perception of menstruation and MHM
  5. To investigate the effect of the MHM intervention on pain management during menstruation

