### iv. 5.4.4 MHM Intervention

All CHIEDZA attendees will have *a choice of one of the following MHM products*: the menstrual cup or reusable pads. This will be accompanied by analgesia (12 tablets of paracetamol or ibuprofen), a bar of soap, a simple period-tracking sheet, and comprehensive MHM education including an MHM educational pamphlet participants can take home and an MHM educational video to be played at the CHIEDZA centre. Clients will be able to ask for a different product but only after 1) a minimum of 3 months of usage and all CHIEDZA female participants who choose an MHM product will have the option of changing their chosen MHM product if they bring the existing MHM product back to the CHIEDZA centre.

Participants in the nested cohort study will be given comprehensive MHM education including an MHM educational pamphlet participants can take home and an MHM educational video to be played at the CHIEDZA centre, a monthly supply of up to 12 analgesics (ibuprofen or paracetamol), a comprehensive period tracking diary, and *all the MHM products* as summarised in Table 5. Participants in the cohort will be recruited from 2 randomly-selected CHIEDZA intervention clusters in Harare and will be followed-up 3 monthly for one year. At enrolment, the 6 month, and 12 month visit, participants will be required to self-complete a questionnaire (using Open Data Kit on a tablet) and at the 3 month and 12 month (endline) visit, participants will be required to hand-in their period tracking diary for review.

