#### v. 5.4.5 Study Outcomes

**Objective 1:** *To understand and describe the current knowledge levels, practices and perceptions around menstruation and MHM among women aged 16 – 24 years in Zimbabwe.*

**Outcome 1:** Qualitative data from the FGDs and descriptive data from the quantitative questionnaire will be analysed with proportion and cross-tabulations to show the distribution of knowledge, perceptions, and practices regarding MHM. Data from the FGDs will complement the quantitative data.

**Objective 2:** *To investigate menstrual product choice, continued use or discontinuation of products, and patterns of use over time among young women offered all 3 product choices*

**Outcome 2:** Menstrual product choice over time amongst young women and proportion of young women with continued or discontinued menstrual product use over time. Data from the FGDs and IDIs will complement the quantitative data

**Objective 3:** *To investigate the effect of the intervention on MHM practices e.g. access and use of clean absorbents, sufficient washing, drying, storage and wrapping of reusable absorbents; washing the body with soap and water*

**Outcome 3:** Using the quantitative data collected from the period tracking diary entries and the pre- and post- quantitative questionnaires, the self-reported MHH practices will be used to generate a pooled, aggregate of adequate MHM practice consistent with the definition given by the WHO and UNICEF and the theory of change model

developed for the longitudinal cohort sub-study intervention. Data from the FGDs and IDIs will complement the quantitative data

**Objective 4:** *To investigate the effect of the MHM intervention on the knowledge and perception of menstruation and MHM*

**Outcome 4:** Pre- and post-intervention quantitative data from the questionnaires will be used to analyse change in the proportion of cohort participants with improved MHM knowledge and perceptions over time

**Objective 5:** *To investigate the effect of the MHM intervention on pain management during menstruation*

**Outcome 5:** Data collected from the period tracking diary and the pre- and post-intervention questionnaires will be used to analyse change in pain management in cohort participants.

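### The Objective 3 endpoint that sizes the 300-woman MHM cohort is inconsistently defined and can be moved by something other than practice

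*Combined protocol and SAP*

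**What the plan says.** Objective 3 (5.4.2) is the effect of the intervention on MHM practices, and it gives "washing the body with soap and water" as one example. The sample size rests on this objective: "300 participants will provide 90% power to detect an increase in adequate HM practices from 10% to a double of 20" per cent, before and after, in the same women.

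Four parts of the plan describe the endpoint.

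- **Definition.** Section 5.4.1 summarises the 2012 WHO/UNICEF definition as clean absorbents (with care of reusables), frequency of change, body washing, disposal and privacy. Statistical Methods in 5.4.7 build a modified aggregate from self-reported practices. They say the intervention will affect three components only: access to clean absorbents, "adequate frequency of absorbent change; and basic understanding of menstruation". Body washing, disposal and privacy are said to be unaffected.
- **Data source.** Outcome 3 (5.4.5) forms the aggregate "Using the quantitative data collected from the period tracking diary entries and the pre- and post- quantitative questionnaires". Statistical Methods assign diary entries to descriptive statistics, including those for Objective 3.
- **Test.** McNemar's test and conditional logistic regression will "compare the proportion with improved MHM practices (Objective 3"), pre and post.
- **Timing.** "At enrolment, consenting participants will receive the MHM intervention including MHM education, analgesics, 2 pairs of period pants" and the products in Table 5. The baseline questionnaire and the first diary belong to the same visit. Follow-up (5.4.7) repeats the same questionnaire at 6 and 12 months and collects diaries at 3 and 12 months.

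**The concern.** The cohort has no control group, so a before-after change can be read as an effect on practice only if the endpoint is fixed, measures practice, and is measured alike at both times. The plan does not secure this.

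The understanding item is taught directly, through the pamphlet, video and education sessions in 5.4.4 and Table 5. It can therefore improve while menstruation is managed exactly as before. Knowledge already has its own objective (Objective 4), and the trial's own good-MHM outcome in 7.1 contains no knowledge item.

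The diary adds a second route. It is first issued at enrolment with the products, so any diary contribution to the aggregate exists only after the intervention.

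Two further conflicts leave the tested quantity open. Objective 3 includes body washing and soap is supplied ("a bar of soap, a simple period-tracking sheet" for all attendees, and soap again in Table 5 for the cohort), yet Statistical Methods say washing will not change. The sample size uses adequate practice, a state that each woman has or lacks at each visit. The test sentence uses improved practice, which has no baseline value.

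At stake is whether a significant result could be reported as a change in practice.

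**Working it through.** **Step 1: the plan's own figure.** From Sample Size (5.4.7): 300 women, 90% power, 10% before and 20% after. Alpha, sidedness, discordance and attrition are not stated. I assume two-sided 5% and independence of the two visits.

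- Discordant cells: p01 = 0.90 × 0.20 = 0.18 and p10 = 0.10 × 0.80 = 0.08, so ψ = 0.26 and d = 0.10.
- McNemar: N = (1.960√ψ + 1.282√(ψ − d²))² / d² = (1.960 × 0.510 + 1.282 × 0.500)² / 0.01 ≈ 269.02, rounded up to 270.
- With an assumed 10% attrition: 269.02 / 0.9, rounded up, is 299, in line with 300.
- Power with 300 evaluable pairs: 92.9% uncorrected, 91.2% with continuity correction, 91.8% exact.
- Sensitivity (exact): 98.1% at a within-woman correlation of 0.3; 87.4% if no woman is adequate at both visits.

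The arithmetic for 300 is sound. The difficulty is what is being counted.

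**Step 2: a rise from understanding alone.** No scoring rule is given. Assume a woman is adequate only if she meets every item, that a fraction A meets the practice items at both visits, and that understanding K is independent of practice. The composite is then A × K, and a move from 10% to 20% needs K to go from 0.10/A to 0.20/A.

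| A | K before | K after | Possible? |
|---|---|---|---|
| 10% | 100% | 200% | No; composite at most 10% |
| 15% | 67% | 133% | No; composite at most 15% |
| 20% | 50% | 100% | Only just |
| 30% | 33% | 67% | Yes |
| 50% | 20% | 40% | Yes |

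The full planned effect can arise without any change in practice only if A is at least 20%.

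**Step 3: diary pooling.** Take 10% positive on the questionnaire at both times.

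- If a diary yes also counts afterwards, the post value is 0.10 + 0.90r. It reaches 20% when r = 0.10/0.90 = 11.1% of questionnaire-negative women.
- If the diary must agree with the questionnaire, the post value falls: at 80% agreement, 0.10 × 0.80 = 8%.

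The direction depends on a rule the plan does not state.

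**Step 4: would an artefact be declared significant?** Exact McNemar with 300 pairs, under the independence assumption of Step 1: a shift from 10% to 20% is significant with probability 0.92, and from 10% to 15% with probability 0.41. If each woman's practice is constant and understanding is only gained (p01 = 0.10, p10 = 0), the probability for 10% to 20% exceeds 0.999.

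**The case against.** The best defence is that a like-for-like comparison is already available. Follow-up specifies the same self-administered questionnaire at baseline, 6 and 12 months, and Statistical Methods keep the diaries descriptive. This stands. A reader might infer that the endpoint is simply a different measure before and after; the documents do not establish that. They establish that 5.4.5 and 5.4.7 conflict on the source.

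A reader might also infer that the word improved makes the baseline zero by construction. The sample size section uses adequate practice with a 10% baseline, and the neighbouring terms in the test sentence describe states (good knowledge, appropriate pain management). It is best read as a wording slip, though one that must be corrected.

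A third inference is that education comes before the baseline questionnaire. The Enrolment text mentions education first but fixes no order. If baseline were taken after teaching, understanding would already be raised, which biases toward no effect.

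Other points also stand. Statistical Methods say which components the intervention affects, not that the other three leave the aggregate. Outcome 3 also refers to the theory of change model, whose figure is not shown. The soap may be meant for cleaning products. Nor do the same problems carry over wholesale to Objectives 4 and 5: Outcome 4 uses questionnaires only, and neither Outcome 5 nor its test is worded as improved.

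What remains is the understanding item in an aggregate described as practices, and the unresolved conflicts over source, washing and wording.

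**Conclusion.** The concern holds as a defect of definition that should be corrected. As written, the endpoint that sizes the cohort can rise through taught knowledge, or move in either direction through post-only diary data, and it has no scoring rule.

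A reader might infer that the planned doubling will appear with no change in practice. The documents support only a conditional version: it needs an all-items rule, understanding independent of practice, and at least 20% of women already meeting the practice items. None of these is stated in the plan. If the conditions held, a cohort of 300 would very probably declare the artefact significant (0.92 or more under the assumptions in Step 4).

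The sample size is not in question, and the issue is confined to this nested, uncontrolled sub-study.

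**What to change.** - In 5.4.5 (Outcome 3) and 5.4.7 (Statistical Methods), define one endpoint: adequate MHM practice, yes or no at each visit. Use practice items only, a stated scoring rule, and the same questionnaire at baseline and 12 months.
- Analyse the understanding item only under Objective 4.
- In the McNemar sentence, replace improved with adequate for Objective 3.
- Keep the diaries descriptive, and correct Outcome 3 to match Statistical Methods.
- Reconcile Objective 3 with Statistical Methods on whether body washing is part of the endpoint.
- In Enrolment, state that the baseline questionnaire is completed before MHM education and products. This is a safeguard, since the text does not currently fix the order.

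The cost is protocol wording and a fixed sequence at the enrolment visit; no new data are needed. If 10% to 20% stays the target, the requirement remains 270 evaluable pairs, or 299 with an assumed 10% attrition, so 300 stands. The downside is that the diary no longer enters the tested endpoint and the measured effect may be smaller.

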### ***Qualitative Methods***

A similar approach will be followed as for the qualitative study as described above (main CHIEDZA study qualitative interviews-see above).

Qualitative FGDs and IDIs will be used to explore the *how* and *why* research questions of the study. FGDs will be used to understand the broad social and environmental context of the study. The FGDs and IDIs will also be used to explore effects of pain during menstruation and the use of analgesics and pain management in general among the women (Objective 5). Semi-structured topic guides for the FGDs and IDIs will also be used to further explore the factors that inform menstrual product choice, continued or discontinued use over time, and

patterns of use (Objective 2) and the effects of the intervention on knowledge levels and perceptions (Objective 4), and MHM practices (Objective 3). Qualitative FGDs and IDIs will also be used to investigate MHM intervention acceptability by looking at affective attitude, burden, ethicality, intervention coherence, opportunity costs, perceived effectiveness, self-efficacy, and intervention implementation challenges (Objective 6).

To adhere to the prevention control measures implemented in the COVID-era, telephonic interviews may become a norm for IDIs (section 5.2.3). Where possible, every effort will be made to obtain written consent, that can be followed up with a phone-based IDIs. However, when not possible, phone-based consent will be sought. Measures to verify true client identity will include 1) video-conference calls where possible with participants 2) asking client name, age & where they stay in the CHIEDZA intervention communities

## ***o. 5.5 STI Screening Acceptability and Effectiveness***

A semi-qualitative study will be nested within CHIEDZA to i) assess current knowledge, attitudes and practices regarding STIs and perceived barriers towards accessing STI testing and partner notification; and ii) determine factors predicting acceptance of STI testing. STI testing will be offered (contingent on availability of test kits) and uptake prevalence and yield of testing will be assessed. .

### ***i. 5.5.1 Background and Rationale***

Youth are a group that is particularly vulnerable to STIs, including syphilis, gonorrhoea, chlamydia, trichomonas and HIV. STIs facilitate HIV transmission and cause morbidity.

Both gonorrhoea and chlamydia can cause pelvic inflammatory disease in women, leading to infertility, risk of ectopic pregnancy or chronic pelvic pain. In Zimbabwe, both are common amongst symptomatic patients. In a study of 200 men with urethral discharge, 73.5% had gonorrhoea, 22.5% had chlamydia, 4.0% had trichomonas and 3.5% had mycoplasma infection, and the prevalence of HIV was 41% among 489 patients presenting with urethral discharge, vaginal discharge or genital ulcer disease.

In LMIC, syndromic management of STIs is the recommended strategy due to resource constraints in implementing aetiological diagnosis. The number of studies assessing the perceptions and acceptability of STI screening is therefore limited. A study in Mombasa (that included only female youth) noted a general willingness for STI screening but barriers included lack of symptoms and stigma The screening for GC, CT and TV within CHIEDZA therefore represents an excellent opportunity to further build on this work to inform us on how to operationalise screening. The limitations of syndromic management were demonstrated in the Zimbabwe study. Among 200 patients with GUD, 27% had GC or CT but most of them did not meet the criteria for concomitant syndromic management. These patients would therefore remain untreated and continue to transmit infection.

Partner notification is integral to effective STI care to reduce infection rates in the population and to prevent both re-infection and the consequences of untreated infections. There are a number of approaches to partner notification, including patient referral (whereby patients are encouraged to contact their sex partners themselves), provider referral (the health care provider notifies the partner and arranges treatment), contractual patient-provider referral (a two-step approach that links patient and provider referral methods), and expedited partner therapy (the diagnosed patient takes the prescriptions or medication to his/her partner)". However, the evidence is not present to identify a single optimal partner notification strategy for a particular STI. Despite the importance of partner notification, it is often not performed adequately. There are a number of potential reasons for this, including concerns about adverse partner reactions, such as risk of violence or of the partner leaving. Embarrassment and stigma are also reported as perceived barriers to partner notification and partner notification is also lower in casual relationships.

### **ii.5.5.2 Study Aim and Objectives**

This sub-study aims to assess current knowledge, attitudes and practices regarding STIs; to assess knowledge, attitudes and perceived barriers towards accessing STI testing and partner notification; and to determine factors predicting acceptance of STI testing. The uptake, yield and prevalence of STI testing will be assessed in the intervention arm. In addition, we will sample a proportion of participants in the endline survey to investigate the impact of offering unselected STI testing on the population level prevalence of STIs.

The objectives are:

1. To assess knowledge, attitudes and practices towards STIs
2. To assess attitudes towards accessing STI testing including site of testing and mechanisms of receiving results
3. To assess attitudes and perceived barriers to partner notification for STIs
4. To determine uptake, yield and prevalence of STI testing
5. To determine factors predicting acceptance of STI testing
6. To determine prevalence of STIs by study arm

